### Recruitment, randomization and blinding

The study will be advertised online via professional websites (i.e., LinkedIn), non- professional social-networks (i.e., Facebook and twitter), and advertisements in newspapers. Furthermore, posters will be placed in local universities (Universitat Jaume I and Universitat de València) and travel agencies. People who are interested will be directed to the research website (www.fobiavolar.es), where they will find further information about the study and what participation entails, as well as an informed consent form. Individuals can request participation through the website and by signing the informed consent form. After website registration, the clinical team will contact participants by telephone to screen for the inclusion and exclusion criteria and explain the research terms (i.e., study design, treatment length, or treatment rationale). Participants who meet the criteria will be administered a diagnostic telephone interview at the time of the screening, or another time will be arranged. Then, participants will be randomly assigned to one of the three experimental groups. The allocation schedule will be generated through a computer randomization program (Epidat 4.0) by an independent researcher who will be unaware of the characteristics of the study. The allocation schedule will be communicated to the study researchers via phone call. Patients will agree to participate before the random allocation and without knowing to which treatment they will be assigned. However, for practical reasons, participants and researchers will not be blind to the treatment conditions. Participants will be free at any time to withdraw from the treatment or the study without giving any explanation.

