### Eligibility criteria

The study sample will consist of adults from 18 years old who meet the Diagnostic and Statistical manual for Mental Health Disorders-Version 5 (DSM-5) (APA, 2013) criteria for specific, situational phobia (FP). They are required to have adequate knowledge to understand and read Spanish, access to the Internet, and the ability to use a computer. Exclusion criteria for the study are as follows: a) receiving psychological treatment for FP; b) diagnosis of a severe mental disorder: abuse or dependence on alcohol or other substances, psychotic disorder, dementia or bipolar disorder; c) presence of depressive symptomatology, suicidal ideation or plan; d) Presence of heart disease; e) Pregnant women (from the fourth month). Receiving pharmacological treatment is not an exclusion criterion during the study period, but any increase and/or change in the medication during the study period will imply the participant’s exclusion from subsequent analyses. A decrease in pharmacological treatment is accepted.

Participants with comorbid and related disorders (i.e., panic disorder, agoraphobia, claustrophobia or acrophobia) will be included when FP is the primary diagnosis. Participants who do not meet the inclusion criteria will be encouraged to seek treatment alternatives better suited to their specific needs.

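### The article has the allocation schedule itself phoned to the study researchers and states concealment for patients only, so its wording does not secure concealment from those who enrol

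*Protocol article*

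**What the plan says.** All of the allocation text is in the protocol article, section Recruitment, randomization and blinding.

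- **Generation.** The schedule is produced by software, "by an independent researcher who will be unaware of the characteristics of the study".
- **Communication.** The next sentence reads: "The allocation schedule will be communicated to the study researchers via phone call".
- **Screening.** After website registration, "the clinical team will contact participants by telephone to screen for the inclusion and exclusion criteria". A diagnostic telephone interview follows, either in the same call or at a later appointment.
- **Order.** After the interview: "Then, participants will be randomly assigned to one of the three experimental groups".
- **Concealment.** "Patients will agree to participate before the random allocation and without knowing to which treatment they will be assigned". There is no matching statement for staff.
- **Blinding.** "participants and researchers will not be blind to the treatment conditions".

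Two entries under Eligibility criteria need some judgement. One is the exclusion for "presence of depressive symptomatology, suicidal ideation or plan", which has no stated threshold. The other is the rule that people with panic disorder, agoraphobia, claustrophobia or acrophobia "will be included when FP is the primary diagnosis".

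**The concern.** Concealment protects a trial up to the moment of assignment: whoever admits, refuses or postpones a candidate must not know the arm that comes next. The article fixes a mechanism for passing on the allocation, and as worded that mechanism does not give this protection.

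If staff know the next arm, borderline candidates can be admitted, refused or deferred accordingly, even without intent. For example, a caller with marked comorbidity might be put off when the next place is in the unguided arm. The arms would then differ at entry for reasons other than chance. Intention-to-treat analysis and multiple imputation do not repair this, because both start from the people who were enrolled. Adjustment for baseline would help only for measured factors, and the ANOVA under Statistical analysis states none. Both the comparison with the waiting list and the guided-versus-unguided comparison would be exposed. The Discussion itself says that the comorbid disorders may affect the outcome measures.

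**Working it through.** **1. What is phoned.** Two consecutive sentences use the same noun. In the first, the allocation schedule is what the software generates, which is the list. In the second, the allocation schedule is what is communicated. Taken at face value, the list is passed on. No sentence says that assignments are released singly.

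**2. When.** The article orders screening, interview and then assignment for each participant. That order does not date the call. If a list is already held, each assignment can follow its own interview while the next arm is known in advance. If one call is made per participant after the interview, the next arm stays hidden. The text fits both.

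**3. To whom.** Screening belongs to the clinical team, and the call goes to the study researchers. The article says neither that these are the same people nor that they are kept apart.

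**4. Who is protected.** Patients are, twice: in the consent sentence, and under Treatment preferences questionnaire, where that form is completed before the participant knows the assigned condition. Staff are not mentioned in either place.

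**5. How much room for judgement.** The Diagnostic interview section specifies the ADIS-IV with DSM-5 criteria, and the Intervention section describes a 19-question screen that covers exclusion criteria. These narrow the discretion. What remains is the ranking of flying phobia against a comorbid disorder, the threshold for depressive symptoms, and the date of the interview.

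**6. Illustration of size.** The documents give no figure to reproduce, so this is a what-if calculation. Inputs:
- the share *p* of candidates kept out of one arm only, taken from the top of the severity distribution: **assumed** 5%, 10% and 20%;
- severity, taken as the baseline score on the scale: **assumed** normal, in SD units;
- retest correlations from Primary outcomes: 0.92 for the FFQ-II (15 days) and 0.86 for the FFS (three months).

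The fall in that arm's mean is φ(z₁₋ₚ)/(1 − p). With no treatment effect, the part carried into the outcome is that fall times the retest correlation.

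| p | Fall in mean (SD) | Carried, FFQ-II (× 0.92) | Carried, FFS (× 0.86) |
|---|---|---|---|
| 5% | 0.1031/0.95 = 0.109 | 0.100 | 0.093 |
| 10% | 0.1755/0.90 = 0.195 | 0.179 | 0.168 |
| 20% | 0.2800/0.80 = 0.350 | 0.322 | 0.301 |

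At 20% the carried shift is about a third of the planned *d* = 1, but that ratio follows entirely from the assumed 20%. Neither retest interval equals the six-week waiting period. Selection exactly from the top of the distribution is an extreme form. The calculation also ignores deferred callers who later enter another arm; they would raise that arm's mean.

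**The case against.** The strongest reply is that the section describes an ordinary, sound procedure in loose words. An independent person generates the sequence, assignment comes after screening and interview, and a telephone call is a normal way to release one assignment. On that reading, *schedule* means only the participant's allocation. A journal article also condenses, and the SPIRIT checklist it cites as Additional file 1 is not shown.

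Much of this stands. The per-participant reading is open, and the order of the section is compatible with it. The structured interview and the screening questions limit discretion. The SD shifts are not evidence of bias in this trial.

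A reader might go further and infer that the unblinded team that decides eligibility holds the list and so knows the next arm when it admits or refuses someone. The article does not support that. It gives different names to the screeners and to the recipients of the call, without saying that they are the same people, and it gives no time for the call. The statement that researchers are not blind concerns knowledge of treatment conditions. It is not evidence that the sequence is known before enrolment, and lack of blinding after assignment is not a failure of concealment.

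The appeal to condensation does not fully answer the point. The article does describe how the allocation is passed on, and the sentence it uses, taken literally, permits advance knowledge. The difficulty lies in what that sentence says, not in detail left to a fuller document.

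**Conclusion.** The point holds in a limited form. As written, the section does not establish allocation concealment from the staff who enrol, and its literal wording would let upcoming assignments be known while eligibility and timing are still being decided. It does not show that they will be known.

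This rests on reading the repeated term as the same object in both sentences, and on the absence of any statement that separates the recipients of the call from the screeners or places the call after the eligibility decision. The size of any bias cannot be estimated from the documents. The range of about 0.09 to 0.32 SD carried into the outcome depends on the assumed shares of 5% to 20%, selected on severity in one arm only. The change is worth making because it costs little and the analysis could not reliably undo the bias it prevents.

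**What to change.** In Recruitment, randomization and blinding, replace the sentence on communicating the schedule with:

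> The independent researcher keeps the allocation schedule and releases by telephone only the assignment of one participant at a time, after that participant's consent, eligibility decision, diagnostic interview and pre-assignment baseline measures (FFQ-II, FFS, secondary clinical scales, preference questionnaire) have been recorded; the schedule is not disclosed to anyone who screens, interviews or treats.

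The expectations scale must stay outside that list. Table 1 counts it as a baseline measure, but the Treatment acceptance measures section has it answered after the rationale of the treatment to be received, with or without support, has been explained. It therefore needs the assignment.

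The second random assignment, after the waiting list, gains little from the same rule, because no new eligibility decision is described there.

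**Cost.** One sentence, and one call per participant; the independent researcher and the telephone route already exist. One practical check is needed: Table 1 has the FFQ-II collected inside the program, so the team should confirm that its assessment part can be completed before assignment. If assignments are already released singly after enrolment, the sentence only records existing practice.

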### Intervention

*NO-FEAR Airlines* is a computer-aided exposure treatment program for FP that can be self-administered via the Internet [53]. This program allows people who are afraid of flying to be exposed to images and sounds related to their phobic fears on a standard personal computer from home. *NO-FEAR Airlines* was developed by LabPsiTec (Laboratory of psychology and technology, Universitat Jaume I, and University of Valencia) in collaboration with LabCDS (University of Balearic Islands). It is a new version based on a previous program *Computer Assisted Fear of Flight Treatment* (CAFFT), created by the LabCSD research group [54, 55], and designed to be completely self-applied over the Internet.

*NO-FEAR Airlines* includes both an *assessment protocol* and a *treatment protocol*. The *assessment protocol* provides a short screening with 19 questions about FP, related problems (i.e., claustrophobia, panic disorder, agoraphobia, and acrophobia), and exclusion criteria. After that, the program carries out a pre-treatment evaluation that includes primary and secondary outcome measures. The *treatment protocol* consists of 3 therapeutic components: psychoeducation, exposure, and overlearning. These three key aspects are based on techniques that have been shown to be effective and conform to recommendations from guidelines on good clinical practice published by international psychology associations such as the American Psychological Association (APA) (www.apa.org) and the National Institute for Health and Clinical Excellence (NICE) (www.nice.org.uk).

The *Psychoeducation* component provides information about what the program will contain, as well as specific information related to FP. Specifically, the program teaches: how many people are affected by the problem; what kinds of people are affected; the physiological, cognitive, and behavioral (or avoidance) components of FP; how it begins and is maintained; and how to cope with the problem. This section contains text, vignettes, and illustrations, in order to make the therapeutic content more attractive to the patient.

*Exposure* is conducted through 6 scenarios composed of images and real sounds related to the flight process: (1) flight preparation, (2) airport, (3) boarding and taking off, (4) the central part of the flight, (5) the airplane’s descent, approach to the runway, and landing, (6) sequences with images and auditory stimuli related to plane crashes. During the exposure scenarios, the system asks (every 3 min) the participant about his/her maximum anxiety level experienced on a scale ranging from 0 “no anxiety” to 10 “high anxiety”. Exposure to each stage ends when the participant indicates an anxiety level lower than 3, in order to achieve the habituation process. Each exposure scenario contains a maximum of 20 cycles (1 cycle consists of images and sounds for 3 min). If the participant exceeds the maximum, the scenario will be presented again at the end. It is possible to take a break from the exposure and between scenarios; however, the program will not advance to the next scenario until the user overcomes the current stage (anxiety level under 3).

#### *Overlearning* component

Additional exposure (to each scenario) in order to achieve overlearning is offered to the patients. They may choose the scenarios they want to confront according to their needs. This component aims to review some of the exposed situations and guarantee/reinforce the achievements. The patient may be exposed to the aforementioned scenarios, but with a higher degree of difficulty because this time, storm conditions and turbulence will be simulated (Fig. 2).

### Instruments

Participants will be assessed at baseline, post-treatment, and 3- and 12-month follow-ups. Assessments will be conducted via call phone, a commercial online survey system (www.surveymonkey.com), and the *NO-FEAR Airlines* program. Both participants and therapists will receive email reminders of each assessment time. The study variables and assessment times are summarized in Table 1.

**Table 1 Tab1:** Study measures, time of assessment, and source of measurement

Measures	Aim	Time of assessment	Source of measurement
ADIS-IV	Diagnosis	BL, post-T and FU	Phone Call
Sociodemographic data	Gender, age, education, occupation, marital status	BL	
FFQ-II	Severity of the FP	BL, post-T and FU	*NO-FEAR Airlines*
FFS	Severity of the FP	BL, post-T and FU	Phone Call
Fear and Avoidance Scales	Fear avoidance, and the degree of belief in catastrophic thought related to the main target behavior.	BL, post-T and FU	Phone Call
Clinician Severity Scale	severity of the patient’s phobia	BL, post-T and FU	Clinician
Patient’s Improvement Scale	Patient’s improvement assessment	BL, post-T and FU	Phone Call
Treatment Preferences Questionnaire	Participant’s treatment preferences	BL, post-T and FU	Phone Call
ESQ	Expectations and satisfaction with the treatment	BL, post-T and FU	Phone Call
*Measures related to flying phobia*	Duration of the problem, flights taken, Safety behaviors, presence of negative experience flying.	BL, post-T and FU	*NO-FEAR Airlines*
Anxiety during exposure	Maximum level of anxiety experienced during the exposure scenarios	During exposure scenarios	*NO-FEAR Airlines*
Cycles of exposure scenarios	Number of cycles in each exposure scenario	After exposure scenarios	*NO-FEAR Airlines*

*BL* Baseline, *Post-T* post-treatment, FU, 3- and 12-month follow-ups; *ADIS-IV* The Anxiety Disorders Interview Schedule for DSM-IV-TR; *FP* Flying phobia, *FFQ-II* Fear of Flying Questionnaire-II, *FFS* Fear of Flying Scale, *ESQ* Expectations and satisfaction Questionnaire

#### Diagnostic interview

The Anxiety Disorders Interview Schedule for DSM-IV-TR (ADIS-IV) [56]. The section on specific phobias will be used. Moreover, DSM-5 criteria will be considered. In cases of comorbidity, other sections of the ADIS-IV (i.e., panic disorder or agoraphobia) will be used. ADIS-IV is an excellent interview for assessing anxiety disorders and has adequate psychometric properties [57].

#### Primary outcomes

The Fear of Flying Questionnaire-II (*FFQ-II*) [58] is a 30-item self-report instrument that describes situations related to flying: anxiety during flight, anxiety experienced getting on the plane, and anxiety experienced during the observation of neutral or unpleasant flying-related situations. For each item, respondents rated their degree of discomfort associated with the situation on a scale from 1 to 9 (1 = not at all, 9 = very much). Scores ranged from 30 to 270. As reported by Bornas et al. [58], internal consistency was *α* = .97, and retest reliability (15-day retest period) was *r* = .92.

The Fear of Flying scale (*FFS*) [59] is a 21-item self-report measure to assess fear associated with various air travel situations. Fear elicited by each situation was rated on a 5-point scale (0 = *not at all*, 4 = *very much*), with scores ranging from 0 to 84. For the original FFS [59], Cronbach’s alpha was .94, and retest reliability (at three months) was .86.

#### Secondary outcomes

##### Socio-demographic variables

The following socio-demographic variables will be collected: gender, age, marital status, educational level, and work status.

##### Other relevant clinical measures

Fear and Avoidance Scales (adapted from Marks & Mathews [60]) are used to assess participants’ fear and avoidance on a scale ranging from 0 (“No fear at all,” “I never avoid”) to 10 (“Severe fear,” “I always avoid”) related to the main target behavior: “flying”. The degree of belief in the catastrophic thought related to the target behavior will also be assessed on a 0 (“*I do not believe the thought at all*”) to 10 (*the thought is totally true*) scale.

The Clinician Severity Scale (adapted from Di Nardo, Brown & Barlow [61]). The clinician rates the severity of the patient’s phobia on a scale from 0 to 8, where *0 = symptom free* and *8 = extremely severe.*

The Patient’s Improvement Scale (Adapted from the Clinical Global Impression scale, CGI; Guy [62]). One item on the CGI scale was adapted in order to assess the level of improvement achieved by the patient (compared to the baseline status) on a 7-point scale (1 “much worse” to 7 “much better”). This scale is answered by the patient.

#### Other measures recorded by the system

##### Measures related to FP

*NO-FEAR Airlines* provides a short assessment of fear and avoidance of flying and checks the following issues: the duration of the problem, how many times the patient has taken a flight, whether safety behaviors were used (e.g., alcohol intake, distraction), and whether the participant has had any negative experiences with flying.

##### Maximum level of anxiety experienced during the exposure scenarios

During exposure to the scenarios, the system asks the user about the maximum anxiety experienced every 3 min, on a scale from 0 “No anxiety” to 10 “maximum anxiety”. The exposure session ends when the anxiety level is less than 3.

##### Number of cycles in each exposure scenario

The *NO-FEAR Airlines* system also records the numbers of cycles participants perform in each exposure scenario. One cycle consists of an exposure duration of 3 min.

#### Treatment acceptance measures

Treatment Expectations and satisfaction scales (adapted from Borkovec & Nau) [63]. This questionnaire measures participants’ expectations before treatment and their satisfaction with it. It includes six items rated from 0 (‘not at all’) to 10 (‘very much’); questions address how logical the treatment seems, to what extent the patient expected to be satisfied with it, whether the patient would recommend the treatment to others, whether it would be useful in treating other problems, the treatment’s usefulness for the patient’s problem, and to what extent it could be aversive. Participants will answer the Expectations scale after the therapist explains the rationale for the treatment they would receive (with or without therapist support) and before beginning the treatment. The satisfaction scale will be completed once treatment is finished. This adaptation has been used in previous studies [64, 65].

##### Treatment preferences questionnaire

This instrument was specifically developed for this research. It is composed of 5 questions designed to measure participants’ preferences about both treatment conditions included in this study (with and without therapist support): (1) Preference (“*If you could have chosen between the two treatments, which one would you have chosen?*”; (2) Subjective effectiveness (“*Which of these two treatments do you think would have been the most effective in helping you to overcome your problem?*”; 3) Logic (*Which of these two treatments do you think would have been the most logical to help you overcome your problem*); (4) Subjective aversion (“*Which of these two treatments do you think would have been the most aversive?*”) and (5) Recommendation (“*Which of these two treatments would you recommend to a friend with the same problem you have?*”). Questions have two response options in accordance with the two treatment conditions. This scale will be completed before participants know the treatment condition assigned and after treatment.

##### Qualitative interview

This interview was also specifically developed for this research. It contains 11 items designed to assess participants’ opinions about the *NO-FEAR Airlines* program and the support received. The interview includes questions rated on a 1 to 5 scale (1 = *very little*; 5 = *very much*) and Dichotomous Questions (“*Yes*” or “*No*”). Additionally, options to extend the participants’ qualitative responses are available.

